# Multipoint Pacing versus conventional ICD in Patients with a Narrow QRS complex (MPP Narrow QRS trial): study protocol for a pilot randomized controlled trial

**DOI:** 10.1186/s13063-016-1698-1

**Published:** 2016-12-03

**Keywords:** Narrow QRS, Multipoint pacing, Cardiac resynchronization therapy, ICD, Heart failure

## Abstract

**Background:**

Despite an intensive search for predictors of the response to cardiac resynchronization therapy (CRT), the QRS duration remains the simplest and most robust predictor of a positive response. QRS duration of ≥ 130 ms is considered to be a prerequisite for CRT; however, some studies have shown that CRT may also be effective in heart failure (HF) patients with a narrow QRS (<130 ms). Since CRT can now be performed by pacing the left ventricle from multiple vectors via a single quadripolar lead, it is possible that multipoint pacing (MPP) might be effective in HF patients with a narrow QRS. This article reports the design of the MPP Narrow QRS trial, a prospective, randomized, multicenter, controlled feasibility study to investigate the efficacy of MPP using two LV pacing vectors in patients with a narrow QRS complex (100–130 ms).

**Methods:**

Fifty patients with a standard ICD indication will be enrolled and randomized (1:1) to either an MPP group or a Standard ICD group. All patients will undergo a low-dose dobutamine stress echo test and only those with contractile reserve will be included in the study and randomized. The primary endpoint will be the percentage of patients in each group that have reverse remodeling at 12 months, defined as a reduction in left ventricular end-systolic volume (LVESV) of >15% from the baseline.

**Discussion:**

This feasibility study will determine whether MPP improves reverse remodeling, as compared with standard ICD, in HF patients who have a narrow QRS complex (100–130 ms).

**Trial registration:**

ClinicalTrials.gov, NCT02402816. Registered on 25 March 2015.

**Electronic supplementary material:**

The online version of this article (doi:10.1186/s13063-016-1698-1) contains supplementary material, which is available to authorized users.

## Background

There is considerable evidence that cardiac resynchronization therapy (CRT) has beneficial effects in heart failure (HF) patients [1, 2]. According to current guidelines, CRT is not recommended if QRS duration is < 130 ms [3]. However, as many as 59% of HF patients with reduced ejection fraction (EF) have a QRS duration of < 120 ms [4]. Although some studies have reported a positive effect of CRT in HF patients with a narrow QRS (<120 ms) [5–7], others have reported that CRT has no benefit in these patients [8]. Recently, a technique for pacing from multiple points in the left ventricle (LV) via a single quadripolar lead has been introduced (multipoint pacing [MPP]). Preliminary studies have demonstrated an acute improvement in LV dP/dt_Max_ [9] and hemodynamic parameters based on pressure-volume loops [10]. Furthermore, MPP has been shown to shorten the QRS duration in comparison with conventional biventricular pacing [11], shorten LV activation time [12], and improve both medium- and long-term outcomes [13, 14]. Pacing from multiple LV sites may improve the response to CRT by capturing a larger area of myocardial tissue, improving depolarization and repolarization patterns, and capturing areas adjacent to scar tissue [15].

Aranda et al. reported that the mean QRS variability may be > 30 ms in patients with HF and a QRS duration ≤ 130 ms [16]. These wide fluctuations in QRS duration over time may be problematic, moving some patients in and out of the CRT indication window. Thus, there may be a “gray zone” of patients with a QRS between 100 and 130 ms who could benefit from CRT. Furthermore, one of the main difficulties in CRT studies in patients with a narrow QRS is that biventricular stimulation in these patients usually results in a QRS that is longer than the baseline QRS. This QRS prolongation may partially offset the potential benefit of CRT in HF patients with a narrow QRS [5].

These patients, with LVEF ≤ 35 and narrow QRS, still have an indication for ICD implantation.

Incidentally, from the MADIT-CRT study results, despite implantable cardioverter defibrillators (ICDs) preventing sudden cardiac death, it does not say that an improvement is obtained in term of ventricular remodeling [17].

In this randomized, prospective, multicenter feasibility trial, we will evaluate the potential benefit of MPP via a quadripolar lead in HF patients with a narrow QRS (100–130 ms) and a standard indication for implantation of an ICD. Patients with no left ventricular contractile reserve, as determined by low-dose dobutamine stress echocardiography test, will be excluded from the study. The control group will consist of patients who receive an ICD only without any CRT. The results of this pilot study could provide important information on the potential benefits of MPP in patients with a narrow QRS complex.

## Methods

### Study population and randomization

This study is a prospective, randomized, multicenter, physician-initiated, pilot study. This is a parallel and superiority study. The study will be conducted at several Italian centers (up to nine high-volume Italian hospitals). Enrollment will begin in 2016 and is expected to continue through the beginning of 2017, until the predefined target number of patients has been reached. The expected duration of the investigation will be approximately 2–3 years, with 24 months of follow-up for each patient. Prior to enrollment, approximately 70–80 patients will be screened by means of an echo-dobutamine stress (DSE) test in order to evaluate the presence of left ventricular contractile reserve. Low-dose dobutamine stress echocardiography (LDSE) is a simple, cost-effective, and widely available method of identifying contractile reserve in the LV [18, 19]. The dose of intravenous dobutamine will be increased in 5 μg kg^−1^ min^−1^ increments every 5 minutes up to a recommended maximum dose of 20 μg kg^−1^ min^−1^. The test will be terminated in the event of arrhythmias or the occurrence of any complications or side effects. Measurements (offline) of end-diastolic and end-systolic volumes will be assessed at each infusion rate by two-dimensional echocardiography (biplane disk method). The left ventricular ejection fraction (LVEF), measured offline by means of Simpson’s biplane quantitative method, will be determined at each infusion rate (including baseline). An absolute increase of 5 points or higher in LVEF above the baseline will demonstrate the presence of LV contractile reserve and will be considered a positive LDSE test [18]. Only patients who have a positive LDSE test will be enrolled if they meet the inclusion criteria reported in Table 1.

**Table 1 Tab1:** Inclusion/exclusion criteria

A. Inclusion criteria
● HF with NYHA class II/III ● LVEF < 35% in patients on OPT for at least 3 months and candidate for ICD ● Patients with left ventricular contractile reserve at low-dose dobutamine stress echocardiography test
● QRS duration: 100–130 ms
● Ability and willingness to comply with study requirements
● Successful quadripolar LV lead implantation (only for treatment group)
B. Exclusion criteria
● Myocardial infarction, unstable angina within 40 days prior to enrollment
● Cardiac revascularization (PTCA, stent or CABG) in the 4 weeks prior to enrollment or planned for the 3 months following enrollment
● Cerebrovascular accident (CVA) or transient ischemic attack (TIA) in the 3 months prior to enrollment
● Primary valvular disease
● Inability to comply with the follow-up schedule
● Age less than 18 years
● Pregnancy or intention to become pregnant during the period of the investigation
● Classification of status 1 for cardiac transplantation or consideration for transplantation over the next 12 months
● Previous cardiac transplantation
● Life expectancy < 12 months
● Permanent atrial fibrillation

*HF* heart failure, *NYHA* New York Heart Association, *LVEF* left ventricular ejection fraction, *OPT* optimized therapy, *ICD* implantable cardioverter defibrillator, *LV* left ventricle, *PTCA* percutaneous transluminal coronary angioplasty, *CABG* coronary artery bypass graft surgery

Patients who meet the eligibility criteria and do not have any exclusion will be recruited by the clinical cardiology groups associated with each enrolling center. Logs will be kept at each center of all identified patients who meet the clinical eligibility criteria. For eligible patients who are not enrolled, the reason for non-enrollment (exclusion) will be recorded.

The enrolled patients will be randomized in a 1:1 fashion to an MPP group or a Standard ICD group (control group).

Randomization will be centralized and stratified by center in order to obtain a balanced distribution of the devices implanted at each center. The random assignment to one of the two study groups will be made by the clinical research organization (CRO) and transmitted to the enrolling clinical center by logging on to a web-based automated program.

A flow diagram of patients in the study and a list of all investigational specific activities/procedures (Additional file 1) are shown in Fig. 1 and Table 2.

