### Implantation procedure

The implantation procedure will be carried out within 30 days of enrollment. All subjects will receive either a market-approved St. Jude Medical (Saint Paul, MI, USA) CRT device that includes the MPP feature (models numbers CD3271-40(Q), CD3371-40(Q), CD3371-40C (QC) or newer) and a St. Jude Medical quadripolar left ventricular lead (Quartet 1458Q or newer) or a market-approved St. Jude Medical ICD device. Any commercially available and CE-marked right atrial and right ventricular leads may be implanted. A Merlin® Patient Care System (model 3650 or newer) programmer will be used to interrogate and program all devices on implantation and during follow-up. Post-implantation fluoroscopic images in two views will be required to document lead locations. Before hospital discharge, patients with an MPP device will undergo A-V delay optimization by means of the Ritter method, in order to maximize diastolic filling [20]. During this session, two MPP pacing vectors will be selected from the quadripolar lead. The pacing vectors will be selected to minimize interventricular conduction delay. Following selection of the two MPP vectors, V-V timing optimization will be performed according to the optimal pacing intervention identified by means of QRS duration criteria to avoid lengthening of the QRS duration. In the ICD group, every physician can decide to implant a ventricular (VVI) or traditional dual-chamber (DDD) ICD, but programming must be VVI 40 bpm [21, 22]. In case of LV lead implant failure the patient will be considered a dropout on treatment analysis.

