### Primary endpoint

The primary endpoint is the percentage of patients who display reverse remodeling in the MPP group, in comparison with the ICD group, at the 12-month follow-up examination. Reverse remodeling is defined as a decrease in LVESV > 15% from the baseline [20].

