### Sample size calculation

A main trial designed to show an effect size of +23% - from a proportion of success of 17% to an expected proportion of success of 40% - with alpha = 5% and power = 90% would require us to enroll 79 patients per group (total 158 patients). In the pilot study, recruiting, randomizing and analyzing 50 participants (25 per group), assuming that 17% approximately four patients) would respond in each group, would produce a 13% upper limit of the one-sided 90% confidence interval; this would exclude us finding a 23% difference, which would be statistically significant in a larger trial. In the event of 10% attrition (23 patients per group enrolled. i.e., incomplete data set due to deviation from protocol, implant failure or missing follow-up) the upper limit of the one-sided 90% confidence interval will be extended to 14.5%. If attrition is higher than 10%, a corresponding increase in sample size will be considered, in order to obtain 45–50 evaluable patients.

Finally, it has been estimated [18] that 30% of the screened patients will have a negative LDSE test. Therefore, about 70–80 patients will be screened for participation in the study, 70% of whom are likely to be enrolled and randomized in the study.

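### Successful LV lead implantation is an eligibility criterion that only MPP patients can fail, and only after randomisation; as written, failures leave the evaluable set and the comparison is not between the randomised groups.

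*Protocol article*

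**What the plan says.** All references are to the protocol article.

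- **Table 1, inclusion criteria:** "Successful quadripolar LV lead implantation (only for treatment group"). The ICD arm has no counterpart.
- **Study population and randomization:** "The enrolled patients will be randomized in a 1:1 fashion to an MPP group or a Standard ICD group (control group"). Table 2 puts both the verification of inclusion and exclusion criteria and the randomisation in the enrolment column. Device implantation comes in later columns.
- **Implantation procedure:** "The implantation procedure will be carried out within 30 days of enrollment". On failure: "In case of LV lead implant failure the patient will be considered a dropout on treatment analysis".
- **Sample size calculation:** the 10% attrition allowance, which leaves 23 per group, is described as "incomplete data set due to deviation from protocol, implant failure or missing follow-up". If attrition is higher, "a corresponding increase in sample size will be considered, in order to obtain 45–50 evaluable patients".
- **Primary endpoint:** "The primary endpoint is the percentage of patients who display reverse remodeling in the MPP group, in comparison with the ICD group", at 12 months.
- **Statistical analysis and decision-making process:** the pilot estimate and its one-sided 90% limit enter the decision to proceed, and the pilot results inform the effect size for the main trial. No analysis population is named there.

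**The concern.** An eligibility criterion should be known before allocation and should apply to both arms. This one does neither. A control patient in whom an LV lead could not have been placed is never identified and stays in the comparison. The same patient allocated to MPP is ineligible under Table 1, a dropout under the Implantation procedure, and attrition under the Sample size calculation. Randomisation then no longer guarantees that the compared groups are alike.

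Two things are at stake. The first is what the estimate means: a response difference among successfully implanted patients is not the difference obtained by allocating patients to MPP, and a feasibility trial of an implanted therapy should carry implant failures in its result. The second is use: an estimate above zero is one of several conditions for proceeding, and the pilot result also informs the main-trial effect size.

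**Working it through.** **Inputs from the protocol article.** Response 17% in controls and 40% with MPP ("from a proportion of success of 17% to an expected proportion of success of 40"%), a difference of 23 points; main trial with alpha 5%, power 90% and 79 per group; pilot with 25 per group, a stated upper limit of 13%, and 14.5% after 10% attrition.

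**Assumptions, because the document gives no figure.** LV lead failure in 1, 2 or 3 of 25 MPP patients (f = 4%, 8%, 12%). Response rate q among failures between 0% and 17%.

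**1. The plan's own figures.** Two-sided comparison of two proportions, pooled variance under the null, no continuity correction:

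n = [1.960·√(2·0.285·0.715) + 1.282·√(0.17·0.83 + 0.40·0.60)]² / 0.23² = (1.251 + 0.791)² / 0.0529 = 78.9, so 79 per group. This matches.

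Pilot limit at zero observed difference, 1.282·√(2p(1−p)/n):
- n = 25: 13.3% (p = 4/25) to 13.6% (p = 0.17); stated 13%.
- n = 23: 14.2% (p = 0.17) to 14.3% (p = 4/23). n = 22.5: 14.4% to 14.6%. Stated 14.5%.

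The limits agree to about half a point. Precision is not the problem: 25 against 23, with both losses in the MPP arm, gives 1.282·√(0.17·0.83·(1/25 + 1/23)) = 13.9%.

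**2. Effect between randomised groups when implanted patients respond at 40%.** Difference = (1 − f)·40 + f·q − 17.

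| Failures of 25 | q = 17% | q = 0% |
|---|---|---|
| 1 (4%) | 22.1 | 21.4 |
| 2 (8%) | 21.2 | 19.8 |
| 3 (12%) | 20.2 | 18.2 |

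Example: f = 12%, q = 0 gives 0.88·40 − 17 = 18.2 points, against 23 among implanted patients. With the formula of step 1, the main-trial size for these differences is 85, 92 and 100 per group (q = 17%) or 90, 104 and 121 (q = 0%), against 79.

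**3. Exclusion when MPP has no overall effect.** Both randomised groups respond at 17%, so the remaining MPP patients respond at (17 − f·q)/(1 − f).
- q = 0%: 17/0.96 = 17.7, 17/0.92 = 18.5, 17/0.88 = 19.3, a spurious difference of +0.7, +1.5 or +2.3 points.
- q = 17%: 17% remains 17%, so no bias.

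**4. The passages side by side.** Table 2 has eligibility verified at enrolment; Table 1 includes an item that cannot be known until implantation, up to 30 days later. These contradict each other whatever the failure rate. The Sample size calculation then computes the attrition-adjusted limit on 23 per group after removing implant failures, although LV lead failure can occur in one arm only.

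**The case against.** **The dropout sentence may concern only a separate on-treatment set, and an unseen SAP may define an all-randomised primary analysis.** The sentence is awkward and, alone, allows that reading. The Primary endpoint section simply compares the MPP group with the ICD group, and the absence of a named analysis set in a condensed article is not a fault. This part stands, so the point rests on what is written. Table 1 makes failed patients ineligible, and the Sample size calculation treats them as incomplete data when it computes the limit behind the pilot decision. An all-randomised analysis in a SAP would contradict both places, which would still need correcting.

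**The bias is small and its direction is not established.** This stands. The documents give neither a failure rate nor a response rate for failures. A shift of 0.7 to 2.3 points is well inside the pilot's 13-point limit and vanishes at q = 17%. The figures in step 2 show the distance between two different quantities, not a bias in either.

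**Stronger readings that the documents do not support.**
- A reader might compute that, with no effect, dropping one non-responding MPP patient raises the chance of an estimate above zero from 42.5% to 57.6%, and call that selection bias. It is mainly tie-breaking. Exact ties have probability 15.1% at 25 against 25, and unequal denominators turn nearly all of them into positive estimates. Dropping one patient who responds at 17%, hence without bias, still gives 55.1%. If a control is lost as well (24 against 24), the figure is 44.9%.
- A reader might infer that the sign of the estimate alone decides whether to proceed. The decision section also requires the upper-limit condition, feasible recruitment and retention, and absence of harm.
- A reader might infer that failed implants are the sicker patients, or that reprogrammed patients are excluded as well. The document says neither.
- The extra recruitment is only to be considered. Adding randomised patients does not itself bias the comparison once everyone randomised is analysed.

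**Conclusion.** The point holds as a defect of stated rules. A criterion that can be failed only after allocation, and only in the MPP arm, defines who is eligible, and the text then removes failures from the evaluable patients. As written, the comparison is not between the randomised groups.

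Its numerical size rests on an assumed 4% to 12% failure rate: a loss of about 1 to 5 points from the 23-point effect (23 − 22.1 = 0.9 at the least, 23 − 18.2 = 4.8 at the most), and 0 to 2.3 points of spurious benefit if there is no overall effect. A bias towards MPP is plausible, not demonstrated. The case for change rests on the broken comparison and on the role of the estimate in planning the main trial, rather than on a large expected distortion.

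**What to change.** 1. Remove the lead-success item from the eligibility criteria in Table 1.
2. State that the primary analysis includes all randomised patients in their assigned arm, with failed implants kept in the MPP group and followed to the scheduled 12-month echo.
3. Keep the on-treatment analysis as a sensitivity analysis.
4. Report the LV lead implant failure rate as a feasibility outcome.
5. Amend the Implantation procedure and Sample size calculation so that implant failure and protocol deviation do not count as attrition when the 12-month echo is available.

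The cost is protocol and SAP wording, plus echo visits for failed-implant patients that are already in the schedule for everyone else. The estimated effect may be slightly smaller, and a main trial planned on it correspondingly larger. The Trial status section reports four patients enrolled, so the change could be made early. It should not wait, because 12-month echoes that were never obtained for failed implants cannot be recovered later.

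### Successful LV-lead implantation is listed as an inclusion criterion but can act only after randomisation and only in the MPP arm; the text points to dropping failed implants from the comparison

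*Protocol article*

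**What the plan says.** All references are to the protocol article.

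- **Eligibility.** Table 1 (Study population and randomization) lists as an inclusion criterion "Successful quadripolar LV lead implantation (only for treatment group". The same section makes Table 1 a condition of enrolment: "Only patients who have a positive LDSE test will be enrolled if they meet the inclusion criteria reported in Table 1".
- **Order of events.** Randomisation comes next: "The enrolled patients will be randomized in a 1:1 fashion to an MPP group or a Standard ICD group (control group". Table 2 puts both the check of the criteria and the randomisation in the enrolment column, and the implants in separate later columns for each arm. The Implantation procedure section gives the interval: "The implantation procedure will be carried out within 30 days of enrollment".
- **Failed implants.** The same section states: "In case of LV lead implant failure the patient will be considered a dropout on treatment analysis".
- **Attrition.** The Sample size calculation section defines its 10% attrition as "incomplete data set due to deviation from protocol, implant failure or missing follow-up", which takes 25 per group down to 23. If attrition exceeds 10%, "a corresponding increase in sample size will be considered, in order to obtain 45–50 evaluable patients".
- **Use of the result.** The Statistical analysis and decision-making section makes an estimate above zero one of several joined conditions for a main trial, and lets the pilot result inform the effect size used to plan it.

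**The concern.** Whether an LV lead can be placed is known only once it has been tried, and it is tried only in patients allocated to MPP. An eligibility rule that depends on it cannot be checked at the time Table 2 assigns to it, and it can never be applied to controls. Patients whose anatomy would defeat the lead leave the MPP group, while their counterparts in the ICD group cannot be identified and remain.

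The analysed groups are then no longer the randomised groups. The pilot would estimate the effect of MPP in patients who turned out to be implantable, set against all controls. A main trial would test a strategy of intending MPP, and failed implants are part of that strategy. With 25 patients per arm, and the pilot result feeding the planning of the main trial, the definition of who is counted should not be left to conflicting passages.

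**Working it through.** **Inputs.** Response proportions come from the Sample size calculation section: "from a proportion of success of 17% to an expected proportion of success of 40"%, that is p_C = 0.17 and p_M = 0.40. Alpha 5%, power 90%, 79 per group for the main trial and 25 per group for the pilot come from the same section. The LV-lead failure fraction f is not given; 5% and 10% are assumed here. The response of failed-implant patients, p_F, is also not given; 0.17 (like controls) and 0 (never respond) are used.

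**Step 1: the plan's own figure.** Two-sided test, pooled variance, no continuity correction, mean proportion 0.285:

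n = [1.960·√(2·0.285·0.715) + 1.2816·√(0.17·0.83 + 0.40·0.60)]² / 0.23² = (1.251 + 0.791)² / 0.0529 = 78.9, so 79 per group.

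The stated figure reproduces. The point does not rest on an arithmetic error.

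**Step 2: MPP works as hypothesised.** With failures dropped, the expected difference is 0.40 − 0.17 = 23.0 points. By randomised arm, the MPP response is (1 − f)·0.40 + f·p_F.

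| f (assumed) | p_F (assumed) | MPP response, all randomised | Difference | Overstatement if dropped | Main-trial n per group |
|---|---|---|---|---|---|
| 5% | 0.17 | 0.95·0.40 + 0.05·0.17 = 0.3885 | 21.85 | 1.15 points | 87 |
| 10% | 0.17 | 0.90·0.40 + 0.10·0.17 = 0.377 | 20.7 | 2.3 points | 96 |
| 5% | 0 | 0.95·0.40 = 0.38 | 21.0 | 2.0 points | 93 |
| 10% | 0 | 0.90·0.40 = 0.36 | 19.0 | 4.0 points | 112 |

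The last column uses the formula of step 1.

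**Step 3: MPP has no effect (17% overall in both arms).** Dropping failures changes the MPP response to (0.17 − f·p_F)/(1 − f). The shift in the difference is:

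| f | p_F = 0 | p_F = 0.17 | p_F = 0.34 |
|---|---|---|---|
| 5% | +0.9 | 0 | −0.9 |
| 10% | +1.9 | 0 | −1.9 |

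The sign depends wholly on the prognosis of failed-implant patients, on which the article says nothing.

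**Step 4: chance of an estimate above zero when MPP has no effect.** Exact binomial, 17% in both arms, number of MPP patients implanted distributed as Bin(25, 1 − f). With 25 against 25 and nobody dropped, the chance is 42.5%, because 15.1% of outcomes are exact ties, which do not count as above zero.

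| f | Failures never respond | Failures respond at 17% (no selection) | Due to selection |
|---|---|---|---|
| 4% | 52.2% | 49.6% | 2.6 points |
| 8% | 56.0% | 50.8% | 5.1 points |
| 12% | 58.0% | 50.1% | 7.9 points |

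Differences are taken before rounding. Between about half and three quarters of the rise from 42.5% occurs with no selection at all: unequal denominators break ties.

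**The case against.** **The handling may be settled elsewhere.** The sentence on failed implants can be read as excluding the patient from an on-treatment analysis only, which would imply that another analysis exists. An article commonly leaves analysis populations to the full protocol or SAP, and neither is shown. This stands as an ambiguity, so the article does not prove that the primary analysis drops these patients. It does not remove the point: Table 1 makes a failed implant an eligibility failure, and the sample size section subtracts it from the evaluable number. An intention-to-treat set named elsewhere would still have to be reconciled with both.

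**The attrition text is not an analysis rule.** It is a precision calculation that reduces both arms equally to 23, and the larger sample is conditional and only to be considered. That is correct. A reader should not infer that failed MPP implants will be replaced one for one.

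**A reader might infer that the comparison is necessarily tilted towards MPP.** The documents do not support this. With no MPP effect, the shift is zero if failures have average prognosis and reverses if theirs is better (step 3). Only under a true MPP effect, with failures responding less well than implanted patients, does dropping them overstate the strategy effect.

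**A reader might also infer that one or two dropped patients decide whether to proceed.** With 4 responders per arm and two non-responding failures dropped, the difference moves from 0 to 4/23 − 4/25 = +1.4 points. That example starts from an exact tie, and missed follow-up in the MPP arm would break it in the same way. An estimate above zero is also only one condition, alongside the upper confidence limit, feasible recruitment and retention, and absence of harm. Shifts of 1 to 4 points are small beside a standard error of √(2·0.17·0.83/25) = 10.6 points.

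**Conclusion.** The point holds in a limited form. The contradiction is explicit: an inclusion criterion that enrolment requires cannot be known until after randomisation, and it applies to one arm. Two further passages point to removing failed implants from the comparison, though neither fixes the primary analysis population beyond doubt. If they are removed, the MPP group is selected and the ICD group is not.

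Under the plan's own hypothesis, the strategy effect is overstated by about 1.2 points at 5% failure and 2.3 points at 10% if failures respond like controls, or by 2 and 4 points if they never respond. These sizes rest on assumed failure rates and assumed responses. A main trial planned on the 23-point difference would have 79 per group, where 87 to 112 would be needed across those scenarios. With no MPP effect, neither the direction nor the existence of a bias can be stated from the documents.

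**What to change.** 1. In Table 1, delete the LV-lead line from the inclusion criteria.
2. In the Implantation procedure section, replace the sentence on failed LV implants with a statement that these patients stay in the MPP group, have LVESV measured at 12 months and are counted by randomised arm in the primary analysis. State that the on-treatment analysis is a sensitivity analysis only.
3. In the Sample size calculation section, remove implant failure from the attrition list.

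The cost is protocol and analysis wording, plus keeping failed-implant patients on the existing follow-up schedule. No extra patients are needed, since those patients now count as evaluable. The drawback is a slightly less favourable MPP estimate if MPP works, by the amounts in step 2. The change should be made early: the article reports four patients enrolled, and a 12-month measurement that is not taken cannot be recovered.
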